**Inclusion criteria**	
Individuals must satisfy the following criteria to be enrolled in the study:	
1. Male or female aged ≥ 18 years at the time of signing the ICF.	
2. Individual must understand and voluntarily sign an ICF before conducting the study-related assessments/procedure.	
3. Willing and able to adhere to the scheduled study visits and other protocol requirements.	
4. Individuals must have been operated with IPAA with a duration of at least 6 month before the screening visit.	
5. Individuals must have a diagnosis of recurrent pouchitis defined as at least two episodes in the last year or relapsing immediately after a reasonable response to antibiotherapy (the antifungal medication is allowed until the day before transplantation).	
6. Individuals must be in remission with a PDAI < 7 at screening	
7. Individuals must have affiliation with a social security system or be a beneficiary of such a system	
8. Women of childbearing age must have a negative pregnancy test at screening and must agree to practice effective methods of contraception	
**Exclusion criteria**	
Individuals who meet any of the following exclusion criteria cannot be enrolled in this study:	
1. Crohn’s disease or indeterminate colitis	
2. Anastomotic stenosis	
3. Individuals with prior treatment by probiotic within 3 months before the transplantation visit	
4. Individuals with prior treatment by corticosteroids within 6 weeks before the transplantation visit	
5. Individuals with prior treatment by immunosuppressors within 3 month before the transplantation visit	
6. Prior treatment with a biologic within 3 month before the transplantation visit	
7. Documented active infection of any kind in the last 6 months	
8. ANC < 1.5 × 10^9^ /L (1500 mm^3^)	
9. Infection with chronic HIV	
10. Pregnant or breastfeeding women	
11. Chronic medical or psychiatric disease that may interfere with the individual’s ability to comply with study procedures	
12. Administration of investigational drugs within 3 months before planned FMT	
13. Adults under guardianship, safeguard justice, or trusteeship	
14. Individuals with difficulty in follow-up (vacation, job transfer, geographical distance, lack of motivation)	
15. Patients with contraindication to colonoscopy or anesthesia (if necessary)	

*ANC* absolute neutrophil count, *FMT* fecal microbiota transplantation, *HIV* human immunodeficiency virus, *ICF* informed consent form, *IPAA* ileal pouch–anal anastomosis, *PDAI* Pouchitis Disease Activity Index

It should be noted that the following drugs, which may interfere with the FMT, are prohibited:
Antibiotics after transplantation;Probiotics in the 3 months before transplantation and for the duration of the study;Immunosuppressive therapy including chemotherapy in the 3 months before transplantation visit;Biologic drugs are prohibited within the 3 months before transplantation visit;Corticosteroids in the 6 weeks before transplantation visit;Nonsteroidal anti-inflammatory drugs (NSAIDs) for the duration of the study.

#### Donors

The University Hospital of Nantes will collaborate with public or private organizations to recruit voluntary donors through public announcements or notices after asking previous donors as part of the care for the treatment of *C. difficile* colitis.

We expect about 100 potential donors to give consent, in order to include 12 donors responding to the selection criteria of the ANSM (French regulatory authority) and considering those lost to follow-up. It should be noted that donors will receive a compensation fee.

It should be noted that as a result of the COVID-19 pandemic, an amendment of the protocol will be made to test the donor and patient for the SARS-CoV-2 virus.

### Study schedule

When including donors in the trial, during the screening visit, the study will be fully explained to the donor and informed consent will be obtained. In the informed consent, the donor will have to give permission (ditto for the patient) to share relevant data with people from the universities taking part in the research or from regulatory authorities and to collect biological specimen for use and storage.

The donors must first meet the criteria of the preselection questionnaire to exclude any contraindications. This preselection questionnaire focuses on digestive disorders, drug treatment, and travel. The donor must then undergo a physical examination by a physician, including examination of the anal margin to search for lesions attributable to human papillomavirus (HPV) or herpes simplex virus (HSV). Blood and fecal testing will then be performed, as these tests are required by the ANSM’s dossier on FMT and its supervision in clinical trials [38] (Table 2). It should be noted that for cytomegalovirus (CMV), Epstein–Barr virus (EBV), and *Toxoplasma gondii*, a sero-concordance with the receiver will be performed.

**Table 2 Tab2:** Infectious disease screening of donors

**Blood test**	
Virology	➢ Human immunodeficiency virus (HIV) ➢ Hepatitis B virus (HBV) ➢ Hepatitis C virus (HCV) ➢ Cytomegalovirus (CMV)^a^ ➢ Epstein–Barr virus (EBV)^a^ ➢ Human T-lymphotopic virus (HTLV)
Bacteriology	➢ Trepenema pallidium
Parasitology	➢ *Strongyloides stercoralis* ➢ *Toxoplasma gondii*^a^ ➢ *Trichinella spiralis* ➢ Amibiasis
**Stool test**	
Virology	➢ Adenovirus ➢ Astrovirus ➢ Calcovirus (norovirus, sapovirus) ➢ Picornavirus (enterovirus, Aichi virus) ➢ Rotavirus ➢ Hepatitis E virus (HEV) ➢ Hepatitis A virus (HAV)
Bacteriology	➢ *Clostridium difficile* ➢ *Listeria monocytogenes* ➢ *Vibrio cholera / Vibrio para-hemolyticus* ➢ Salmonella ➢ Shigella ➢ Yersinia ➢ Campylobacter ➢ Multiresistant bacteria to antibiotics
Parasitology	➢ Strongyloïdes stercoralis ➢ Cryptosporidium sp. ➢ Cyclospora sp. ➢ *Entamoeba histolytica* ➢ Giardia intestinalis ➢ Isospora sp. ➢ Microsporidies ➢ Blastocystis hominis ➢ *Dientamoeba fragilis*

^a^ Sero-concordance with the receiver

The main inclusion criteria for the donors are: adults of both sexes (aged 18–65 years) with a body mass index of 17–30 kg/m^2^ and a usually regular transit of 1–3 stools per day corresponding to types 2–4 on the Bristol scale.

The non-inclusion criteria for the donors are divided into three classes relating to the patient’s status, previous or concomitant treatment, and infectious risk, and these are provided in Tables 2 and 3.

**Table 3 Tab3:** Exclusion criteria for the donor

**1 Exclusion criteria related to general safety**	
*Personal status*	
*General*	➢ Presence of chronic disease ➢ Pregnant or lactating women ➢ Adults under guardianship, safeguard justice, or trusteeship ➢ For donors over the age of 50 years, absence of screening test for colorectal cancer within 2 years and positive test result
*Digestive*	➢ Celiac disease ➢ Irritable bowel syndrome ➢ Chronic constipation ➢ Diarrhea defined as > 3 very soft or liquid stools per day ➢ Hemorrhoids or rectal bleeding ➢ Personal history of: • gastrointestinal neoplasia or polyps • autoimmune or inflammatory disease • IBD
*Diet and drug use*	➢ Particular diet (exclusion diet, vegetarian diet) or other specific considerations: ingestion of a potential allergen (e.g. peanut) to which the recipient has a known allergy ➢ → Alcohol or drug abuse ➢ Spouse of a patient with IBD
*Family status*	➢ First-degree family history of: • IBD • gastrointestinal neoplasia or polyps before the age of 60 years • autoimmune or inflammatory disease ➢ Diarrhea defined as > 3 very soft or liquid stools per day for the family members within 3 months.
**2 Exclusion criteria related to prior or concomitant treatment**	
	➢ No medication whatsoever in the 48 h before the donation (except contraceptive treatment) ➢ No regular curative medication except oral contraception ➢ Immunosuppressants (e.g. calcineurin inhibitors, corticosteroids, biological agents, etc.) antineoplastic chemotherapy ➢ Antibiotic or antifungal in the previous 3 months before the donation ➢ Non-steroidal anti-inflammatory intake in the previous month for the donation
**3 Exclusion criteria related to infection risk**	
*General*	➢ Abnormal macroscopic appearance of stool ➢ Known infection by HIV, HTLV virus, hepatitis B or C virus ➢ Positive result in one of the contagious disease testing (see Appendix ANSM) ➢ Existence of anal lesions suggestive of viral infection (papillomas, vesicles, or other lesions) ➢ Multiresistant bacteria carrier (see Appendix ANSM) ➢ Risk of Creutzfeldt–Jakob disease ➢ Personal history of typhoid fever
*2 years*	➢ Residence in the intertropical zone > 2 years
*12 months*	➢ Hospitalization abroad > 24 h in the last 12 months (including members of the family)
*6 months*	➢ Contact with human blood (blood transfusion, piercing, tattoo, etc.) within the previous 6 months ➢ Sexual behavior risk (defined as unprotected sexual contact with a new partner) in the previous 6 months
*3 months*	➢ Gastroenteritis in the last 3 months Digestive disorders such as acute or chronic diarrhea in the 3 months preceding the donation ➢ Behavior deemed at risk of infection: travel in the previous 3 months
*14 days*	➢ Infectious episode 14 days before screening
**Blood tests**	
*Biology*	➢ Abnormal local lab value concerning the following tests: fasting glucose, blood count, platelets, ferritin, CRP, ionogram, urea, creatinine, AST/ALT, gamma glutamyl transferase, alkaline phosphatase, bilirubin, prothrombin time, activated partial thromboplastin time, lipids (cholesterol, triglycerides)
*Virology, bacteriology, and parasitology*	See Table 2
**Stool test**	
*Virology, bacteriology, and parasitology*	See Table 2

*CRP* C-reactive protein, *HIV* human immunodeficiency virus; *IBD* Irritable Bowel Syndrome

As with patients, certain treatments are prohibited to donors before fecal donation:
Antibiotic or antifungal in the 3 months preceding the donation;NSAIDs in the month preceding the donation;Immunosuppressive drugs (e.g. calcineurin inhibitors, corticosteroids, biological agents, etc.) for antineoplastic chemotherapy in the 3 months preceding the donation;Any medication in the 48 h preceding the donation (except contraceptive treatment).

### Randomization

Forty-two of the individuals who respond after 4 weeks of antibiotherapy will be randomized at a ratio of 1:1 to receive either FMT or sham transplantation.

The randomization will be carried out via the Ennov Clinical website: https://nantes-lrsy.hugo-online.fr/CSOnline/ by the study nurse. This randomization process is not stratified by any factors such as age, gender, or center.

However, in addition to the randomization described above, a sero-concordance of CMV, EBV, and *toxoplasma gondii* status between donor and receiver will be required.

### Fecal microbiota or sham transplantation

#### Donor preparation

All healthy donors will be recruited by the University Hospital of Nantes. Donors will be screened in accordance with ANSM recommendations, as described above [38]. The donors’ feces will be collected in a special collection system and always transported on ice. The trial schedule of the donor is showed in Table 4. Processing will be carried out under aerobic conditions. The stools will be weighed to determinate the optimal quantity for the screening tests, safety samples, and transplant preparation. If the stool weight is insufficient (< 70 g), the stool donation will be used for the screening tests and safety samples and the donor will be asked to come back within 15 days for a second stool donation.

**Table 4 Tab4:** Study schedule for the donor [39]

Study procedures	Screening^a^	Inclusion^a^	1 month Call + or – 14 days
Written Informed Consent	X		
Review of Inclusion / non inclusion Criteria	X	X	
Digestive Status	X	X	
Medical History & Demographics	X		
Physical Exam	X	X	
Vital Signs	X	X	
Blood (safety ANSM)		X	
Stool samples, donation stool (safety ANSM)		X	
Fecalotheque		X	
Concomitant treatment	X	X	
Screening survey	X		
Lightened survey		X	
Safety survey			X

^a^The screening and the inclusion visit could be made at the same time

The preparation will be carried out under the hood: donors’ stools will be mixed in sterile saline without preservatives using a commercial blender to obtain a final concentration of 0.5 g feces/mL. We have therefore opted for a single-use system (containing the saddle and mixing shaft), thus eliminating any risk of cross-contamination.

Materials will be filtered with sterile gauze to obtain a solution without particulate material. The suspension in the container will be prepared using pharmaceutical-grade glycerol as a bacterial cryoprotectant at a final concentration of 10%. The solution will then be placed in 30-mL syringes directly adaptable on the channel of the colonoscope and stored frozen at – 80 °C for a maximum of 365 days [40–44]. All the syringes will be identical and opaque to ensure blinded conditions. The placebo will be sterile saline with pharmaceutical glycerol at a final concentration of 10% in sterile syringes directly adaptable on the channel of the colonoscope.

#### Administration plan

The investigational medicinal product (the Pharmacy will be the only one aware if it is fecal microbiota suspension or placebo) should be administered under the close supervision of an experienced physician and in an environment where full resuscitation facilities are immediately available.

On the day of the transplantation, three 30-mL syringes (two syringes plus a back-up syringe, all either donor or placebo) will be left at room temperature for 2 h to defrost. The contents of the two syringes will be injected 10 cm above the pouch. Finally, a 30-mL syringe of sterile saline will be administered into the pouch to push the fecal solution and avoid waste of FMT.

It should be noted that the randomized individuals will continue antibiotherapy until 48 h before transplantation and will undergo a bowel cleansing (2 L of polyethylene glycol) the night before the FMT and will fast from midnight.

After transplantation, the patient will stay in the left decubitus position for 2 h and then the dorsal decubitus position for 2 h. Four hours after the transplantation, the patient will have a collation; clinical surveillance will continue for 6 h after transplantation to allow vital signs to be monitored (temperature, pulse, blood pressure) every 2 h.

After which, patients will return for visits 2, 6, 12, 18, and 24 months after transplantation, as shown in Fig. 1.

**Fig. 1 Fig1:**
[figure not shown]
Study diagram

During each visit, physical examination results, adverse events (AEs), and concomitant treatments will be recorded, and Pouchitis Disease Activity Index (PDAI) [45] and IBD Disability Index [46] questionnaires will be filled in. The patient flow chart can be seen in Table 5.

**Table 5 Tab5:** Study schedule for the patient [39]

Study procedures	V1 Week -2 Screening + or - 3 days	Week -1 Randomisation	V2 Week 0 Transplantation	V3 Week 8 + or - 3 days	V4 Week 24 + or - 7 days	V5 Week 52 + or - 7 days	V6 Week 104 + or - 7 days	Unscheduled Visit (relapse)
Written Informed Consent	X							
Review of Inclusion, non inclusion Criteria	X	X						
Medical History (including UC disease history) & Demographics (including initials, date of birth, sex, tobacco status)	X							
Pouchitis caracteristics and treatments	X							
Physical Exam	X			X	X	X	X	X
PDAI	X			X	X	X	X^a^	X
IBD-Disability Index	X		X	X	X	X	X	X
Flexible rectosigmoïdoscopy (FS)	X		X	X	X	X		X
Biopsies	X (2)^b^		X (4)^c^	X (6)^b+c^	X (6)^b+c^	X (6)^b+c^		X (7)^b+c+d^
Vital Signs	X		X	X	X	X	X	X
Blood samples : blood count, CRP	X^e^		X	X	X	X		X
Biotheque receiver (serum)			X					
Stool Samples (*Clostridium difficile* toxin, parasite)								X
Stool Samples Fecalotheque^f^			X	X	X			X
Prolongation of ATB until 48h prior to the transplantation	X							
Fecal microbiota transplantation/ sham transplantation			X					
Adverse events			X	X	X	X	X	X
Concomittant treatment	X		X	X	X	X	X	X

a: clinical PDAI

b: histology

c: tissutheque

d: CMV

e: Serology will be proceed to check the sero-concorance with the donor (CMV, EBV and toxoplasma gondii)

f: stool samples will be collected before the colonic preparation

Since these visits are not part of routine care, patients will be financially compensated for each visit.

Furthermore, a donor feces biocollection (fecalotheque donor) and a patient biopsy (tissutheque), serum (biotheque) and feces biocollection (fecalotheque receiver) will be centralized at Nantes University Hospital (CHU Nantes) to evaluate the correlation between donor and patient microbiota before and after FMT. The delay of the possible patient’s microbiota resilience after FMT will be constituted. These biocollection samples will be used in future ancillary studies.

## Objectives and statistics

### Objectives

The main objective of the present study is to compare the relapse delay after FMT versus sham transplantation for recurrent pouchitis in IPAA for UC.

The secondary objectives are:
Efficacy of FMT on the rate of relapse at week 24;Efficacy of FMT on the rate of relapse at week 52;Instauration of alternative treatment within week 52;Safety of FMT in cases of pouchitis;Modifications of the fecal microbiota of a patient with ileal pouch for UC complicated by recurrent pouchitis, in remission after antibiotherapy after FMT from a healthy donor at week 8;Evolution of health-related disability.

### Endpoints

The primary endpoint is the delay between the date of transplantation and the date of the clinical and endoscopic relapse defined by a PDAI ≥ 7 points.

The PDAI is a 19-point index of pouchitis activity based on both clinical symptoms and endoscopic and histologic findings [45]. Active pouchitis is defined as a PDAI ≥ 7 and remission is defined as a PDAI < 7. Clinical response to treatment can also be quantified by reduction in the PDAI (e.g. a reduction in the PDAI score ≥ 3 from baseline).

The secondary endpoints are:
Relapse at week 24 defined as a PDAI ≥ 7 at week 24;Relapse at week 52 defined as a PDAI ≥ 7 at week 52;Delay within the transplantation and the instauration of an antibiotherapy or alternative treatment (immunosuppressive and/or biotherapy and/or corticotherapy);Register of AEs defined by Common Terminology Criteria for Adverse Events (4.3) 104 weeks after transplantation according to ANSM recommendation;Fecal microbiota engraftment at 8 weeks defined by: Sorensen’s index ([receiver 8 weeks after FMT vs donor] > Sorensen’s index [receiver 8 weeks after FMT vs receiver before FMT]) with Sorensen’s index (receiver 8 weeks after FMT vs donor) = 0.6. To assess this endpoint, fecal microbiota composition will be analyzed for donor sample, receiver sample before FMT and 8 weeks after FMT, using 16S sequencing (Illumina Miseq technology);IBD Disability Index at weeks − 5, baseline, and weeks 8, 24, and 52 and unscheduled visit.

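### The week-8 engraftment endpoint sets donor similarity equal to 0.6 instead of at least 0.6, so the result depends on how one sign is read

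*Protocol article*

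**What the plan says.** All references are to the protocol article.

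- **Endpoints, secondary endpoints.** Engraftment at 8 weeks requires the Sorensen index between the week-8 stool and the donor to exceed the index for "receiver 8 weeks after FMT vs receiver before FMT". It adds a value for the donor index: "receiver 8 weeks after FMT vs donor) = 0.6". No tolerance, rounding rule or inequality accompanies the 0.6.
- **Endpoints, samples.** "fecal microbiota composition will be analyzed for donor sample, receiver sample before FMT and 8 weeks after FMT", by 16S sequencing. No donor reference is named for a patient who receives sham.
- **Objectives.** The microbiota objective concerns change in patients "in remission after antibiotherapy after FMT from a healthy donor at week 8", so it is worded for FMT.
- **Donor preparation.** The sham contains no donor material: "The placebo will be sterile saline with pharmaceutical glycerol at a final concentration of 10% in sterile syringes".
- **Administration plan.** "the randomized individuals will continue antibiotherapy until 48 h before transplantation"; bowel cleansing follows on the eve of the procedure.
- **Table 5.** One schedule serves both arms. Stool for the biocollection is listed at weeks 0, 8 and 24 and at relapse. Footnote f says "stool samples will be collected before the colonic preparation".

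**The concern.** A similarity cut-off normally works as a floor. Written as an equality, it admits a single value of an index that can take many, and it excludes patients on both sides of that value, including those most like the donor. If a programmer followed the text, the trial would report almost no engraftment whatever the transplant did. If the analyst chose a rounding or a direction after seeing the data, the engraftment rate would depend on that choice.

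A smaller issue lies in the first condition. Its comparator is the patient's own stool at about the end of antibiotic treatment. If the flora recovers once antibiotics stop, the week-8 sample may move away from that baseline with or without a transplant. This would make it easier for donor similarity to exceed baseline similarity. The article does not describe using sham patients to show how often that happens.

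**Working it through.** **The plan's own figure.** The 0.6 is given without derivation, so there is nothing to reproduce. The article's computed design figure belongs to the primary endpoint: HR = ln(0.60)/ln(0.25) = 0.3685, and Schoenfeld's formula with 80% power and an assumed two-sided 5% level gives 32 events, as stated. The present point does not touch it.

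**Is the sign a text-extraction fault?** The same section prints its other inequality signs correctly: "Active pouchitis is defined as a PDAI ≥ 7 and remission is defined as a PDAI < 7". Loss of the sign in reading the PDF is therefore not a clear explanation. The equals sign is either the published text or a slip in it.

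**When exact equality is possible.** With A and B taxa in the two samples and C shared, S = 2C/(A + B). Setting S = 0.6 gives 10C = 3(A + B). So A + B must be a multiple of 10, and C must be exactly 0.3(A + B).

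**How often it is met.**
- From the article: 42 randomized 1:1, so about 21 in the FMT arm.
- Assumed, because the article gives no values: 50–150, 100–300 or 200–500 taxa per sample; S with mean 0.4 to 0.7 and SD 0.10, or mean 0.6 and SD 0.05. One million simulated pairs per scenario.

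Expected number of 21 FMT patients who meet the 0.6 condition alone (range over the three richness bands):

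| Mean S (SD) | Exactly 0.6 | 0.60 after rounding to two decimals | 0.6 after rounding to one decimal | ≥ 0.6 |
|---|---|---|---|---|
| 0.4 (0.10) | 0.003–0.011 | 0.11–0.12 | 1.3 | 0.5 |
| 0.5 (0.10) | 0.014–0.053 | 0.51 | 5.1–5.2 | 3.2–3.3 |
| 0.6 (0.10) | 0.025–0.093 | 0.87–0.89 | 8.3–8.5 | 10.0–10.4 |
| 0.7 (0.10) | 0.017–0.066 | 0.56–0.64 | 5.6–6.3 | 16.8–17.6 |
| 0.6 (0.05) | 0.052–0.176 | 1.68–1.71 | 14.4–14.5 | 10.0–10.5 |

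Under strict equality 0.02% to 0.84% of patients qualify. The chance that none of 21 qualifies is (1 − 0.0084)^21 = 84% in the most favourable scenario and above 99% in the least. Requiring the first condition as well can only lower these counts.

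The rows for mean 0.6 and 0.7 (SD 0.10) show the defect best. As the arm becomes more like the donors, every equality reading gives fewer engrafted patients, while the minimum gives more.

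**Hand check.** With S spread evenly over 0.45–0.75, a two-decimal match has probability 0.01/0.30 = 3.3% (0.7 of 21), a one-decimal match 0.10/0.30 = 33% (7 of 21), and S ≥ 0.6 has 0.15/0.30 = 50% (10.5 of 21).

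**Timing of the baseline stool.** Antibiotics run to 48 h before transplantation, cleansing is on the eve, and stool is collected before cleansing. The week-0 sample is therefore taken on antibiotics or within about 48 h of their end. The drug restrictions below Table 1 prohibit antibiotics after transplantation, so by plan the two samples differ in antibiotic exposure in both arms.

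**The case against.** **The sign is an obvious slip.** Next to a condition written with a greater-than sign, most readers would take 0.6 as a floor, and it is one character in one mechanistic secondary endpoint. This is probably what was meant, and it limits the weight of the point. The published definition still says something else, and a decision threshold should not rely on charitable reading.

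**Almost no engraftment holds only for strict equality.** This stands. At one decimal, the precision in which the cut-off is printed, up to 14.5 of 21 could qualify. The claim is therefore that the result depends on the reading, not that it will be near zero.

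**A reader might infer that the endpoint cannot be computed in sham patients.** The documents do not support that. Table 5 schedules week-0 and week-8 stool in one table for both arms, so the own-baseline index is available, and the donor index lacks only a rule naming the reference donor. Nor do they show that a particular donor is assigned to a sham patient at screening. Footnote e of Table 5 says only that serology is done to check concordance.

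**A reader might infer that the engraftment rate is simply confounded by antibiotic recovery.** That goes too far. Recovery bears mainly on the first condition, and a minimum donor similarity gives partial protection. The article gives no size for the effect. Engraftment is by nature an FMT-arm measure, the objective is worded that way, no between-arm test of it is described, and a sham comparison may sit in the full protocol or analysis plan, which are not shown. The sham reference is therefore an improvement, not the correction of an error.

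**Conclusion.** The equality is wrong as written and should be corrected. Taken strictly, it would classify fewer than 1% of FMT patients as engrafted (0.003 to 0.18 expected of 21) and reject those most similar to the donor. Looser readings give about 0.1 to 1.7 (two decimals) or 1.3 to 14.5 (one decimal). These counts rest on assumed richness and similarity distributions and show sensitivity to the reading; they do not predict the trial's result. That the sign is wrong does not depend on them.

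The antibiotic timing is a secondary matter. It follows from the schedule, its size is unknown, and it is partly guarded by a minimum threshold. The primary endpoint, its log-rank test and the 32 events are unaffected.

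**What to change.** 1. In Endpoints, state the donor-similarity cut-off as a minimum (Sorensen index, week 8 versus donor, ≥ 0.6), applied to the unrounded index and required together with the first condition. This costs a wording change. Trial status reports no patients included at the time of writing, so it could be made before any data existed.
2. Optional, and secondary: choose one of the following.
   - Compute both indices in sham patients against a pre-specified reference, for example the mean over sero-concordant donors in the bank (the Donors section plans 12 donors), and report them by arm. For that comparison use the same reference in the FMT arm, since a mean over several donors is not equivalent to an index against a single donor. The stool is already scheduled. The cost is sequencing about 21 × 2 = 42 sham samples, if this is not already planned.
   - State that the endpoint is descriptive in the FMT arm only, and that it does not separate donor transfer from recovery after antibiotics. This costs one sentence.
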